
### Process evaluation

The process evaluation will be conducted in intervention schools twice through the program period to monitor and document the level of implementation of Health Lifestyles Interventions. Moreover, it also aimed to assess the factors that may have influenced its effectiveness and to record stakeholders’ suggestions for future improvements. Based on the steps and principles described in the conceptual framework by Saunders et al. [21], we identified and assessed the process evaluation elements as following: (1) Recruitment/Reach: the recruitment procedure was monitored against the standardized protocol of the study, the proportions and the characteristics of school/teachers/families agreeing to participate in the intervention and completing or dropping out from the intervention were recorded; (2) Dose delivered (completeness): the intensity of actual implementation of the program was assessed; (3) Fidelity: the extent to intervention was implemented as initially planned was assessed;(4) Dose received (exposure and satisfaction): the extent to which children/parents/caregivers/teachers were exposed to the intervention, as well as the degree of their satisfaction with the intervention and material were assessed; (5) Context: several physical (e.g. weather conditions, school infrastructure and curriculum), social (e.g. socioeconomic status of the family, teachers’ health-related behaviors) and contextual (e.g. policies) factors that may have acted as barriers or facilitators to the implementation of the intervention were recorded. Based on the targeted assess element and practical issues [22], the process evaluation methods were designed to include mainly quantitative methods for researchers, teachers and parents: (1) Look up Teachers’ monthly logbooks; (2) Direct regular observation during the implementation of the classroom activities; (3) Regular qualitative interviews of focus groups. Assessed questionnaires and sampling methods have been developed for children, families and schools.

### Statistical analyses

#### Quantitative data analyses

Descriptive statistics were calculated. Between group difference was examined for treatment assignment and overweight status. Differences were tested using independent t-tests for continuous variables (e.g., BMI, blood sample outcomes) and chi-square tests for categorical variables (e.g., overweight, lifestyle factors and obesity related knowledge). Multilevel regression models will be used to test for post-test group differences on the main outcome variables corrected for pre-test measurements. Data will be double entered and cleaned with EpiData 3.0, and managed and analyzed using SPSS 13.0. P < 0.05 is used to assess statistical significance.

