**Methods/Design:**

The study was designed as a national multi-centered cluster randomized controlled trial involving more than 70,000 children and adolescents aged 7–18 years from 7 provinces in China. In each center, about 12–16 primary and secondary schools, with totally at least 10000 participants were randomly selected (Primary: Secondary = 1:1). All of the selected schools were randomly allocated to either intervention or control group (Intervention: Control = 1:1).The multi-components school-based and family-involved scheme was conducted within the intervention group for 9 month, while students in the control group followed their usual health practice. The intervention consisted of four components: a) Create supportive school and family environment, b) Health lifestyles education and related compulsory physical activities, c) Instruct and promote school physical education, d) Self-monitor obesity related behaviors. Four types of outcomes including anthropometric, behavioral, blood chemical and physical fitness were measured to assess the effectiveness of the intervention program.

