### Sample size calculations

The target sample size was calculated to detect a difference of 10% obesity prevalence between the intervention and control groups (defined by using WGOC criteria) [19] at 9 months, the minimum number required would be 420 of each grade in each center, the sample size of 70000 students from 70 schools located in7 centers has 90% power to detect a significant difference in obesity prevalence. Statistical significance is set at 5% (two-sided).

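### Student-level t-tests and chi-square tests are stated for arm differences in a school-randomised trial, beside multilevel models limited to undefined main outcomes, with no rule on which test decides

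*Protocol article*

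**What the plan says.** The unit of randomisation is the school. The abstract of the Protocol article states: "All of the selected schools were randomly allocated to either intervention or control group". The section on randomization and blinding agrees, and adds stratification by district, school level and school size.

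The paragraph on quantitative data analyses then does three things in turn. It says that descriptive statistics were calculated and that groups were compared both by allocated arm and by overweight status. It names the tests for those comparisons: "Differences were tested using independent t-tests for continuous variables (e.g., BMI, blood sample outcomes) and chi-square tests for categorical variables (e.g., overweight, lifestyle factors", a list that ends with obesity-related knowledge. It then plans the effectiveness analysis: "Multilevel regression models will be used to test for post-test group differences on the main outcome variables corrected for pre-test measurements". One threshold closes the paragraph: "P < 0.05 is used to assess statistical significance".

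The paragraph does not say at which time point the simple tests apply, which outcomes count as main, or which result stands if a simple test and a multilevel model disagree. Under specific objectives, the primary outcome is the change in prevalence of overweight and obesity. The secondary outcomes cover anthropometry, behaviour, five blood measures and physical fitness.

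**The concern.** Independent t-tests and Pearson chi-square tests treat each student as an independent observation. Students in one school share catchment, canteen, timetable and staff, and the whole school receives one allocation. The variance of an arm difference is then larger than these tests assume, so their P-values are too small and their confidence intervals too narrow.

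The multilevel sentence deals with this for the outcomes it covers. It leaves two gaps. If the main outcomes are the primary ones only, then waist, blood pressure, lipids, fitness and behaviour have the student-level tests as their only stated between-arm analysis. And because overweight is named among the chi-square variables and is also part of the primary outcome, it could be reported with two P-values, one of them invalid, with nothing fixed in advance about which counts. The discussion section says that the results could justify a national school programme, so false claims of benefit on these outcomes would matter.

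**Working it through.** **Inputs**

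- Significance level: "Statistical significance is set at 5% (two-sided"), from the sample size section.
- Students per school, *m*. The sample size section gives "the sample size of 70000 students from 70 schools located in7 centers has 90% power to detect a significant difference in obesity prevalence", so *m* = 70,000 / 70 = 1,000. The participants section instead gives 12 to 16 schools in each of 7 centres, that is 84 to 112 schools, so *m* = 70,000 / 84 = 833 down to 70,000 / 112 = 625. Both ends are carried through.
- ICC: not in the article. The range 0.001 to 0.02 is my assumption.

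**The plan's own figures.** The article states no ICC, design effect or false-positive rate, so there is no figure of its own to reproduce on this point. Its sample size figure ("the minimum number required would be 420 of each grade in each center") cannot be checked without a control-arm prevalence, and it is not used below.

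**Formulae**

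- Design effect: DE = 1 + (*m* − 1) × ICC.
- True size of an unadjusted two-sided 5% test: 2 × [1 − Φ(1.96 / √DE)].

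Worked case, *m* = 1,000 and ICC = 0.01: DE = 1 + 999 × 0.01 = 10.99; √DE = 3.3; 1.96 / 3.315 = 0.591; size = 2 × [1 − Φ(0.591)] = 55.4%.

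| Assumed ICC | DE, *m* = 1,000 | True size, *m* = 1,000 | True size, *m* = 833 | DE, *m* = 625 | True size, *m* = 625 |
|---|---|---|---|---|---|
| 0.001 | 2.00 | 16.6% | 14.8% | 1.62 | 12.4% |
| 0.005 | 6.00 | 42.3% | 38.8% | 4.12 | 33.4% |
| 0.01 | 10.99 | 55.4% | 52.1% | 7.24 | 46.6% |
| 0.02 | 20.98 | 66.9% | 64.1% | 13.48 | 59.3% |

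**Check by simulation.** Beta-binomial data with no true effect, 70 schools of 1,000, an assumed prevalence of 15%, 20,000 runs and no stratification gave rejection rates of 4.9% at ICC 0, 16.4% at 0.001, 42.4% at 0.005, 55.1% at 0.01 and 66.7% at 0.02. These agree with the formula.

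**Where the rate reaches one half.** This needs 1.96 / √DE = 0.6745, so DE = 8.44. Then ICC = 7.44 / 999 = 0.0075 for *m* = 1,000, and 7.44 / 624 = 0.012 for *m* = 625.

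**Interval width.** The unadjusted interval is too narrow by a factor of √DE. At ICC 0.01 that is about 3.3 for *m* = 1,000 and √7.24 = 2.7 for *m* = 625.

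**Blood measures.** Blood sampling had its own section in the consent forms, so fewer students per school may contribute. With an assumed 100 per school and ICC 0.01, DE = 1 + 99 × 0.01 = 1.99 and the true size is about 16%.

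**The case against.** The strongest reply is that the effectiveness analysis is already cluster-aware. The multilevel sentence is the only one that mentions post-test arm differences, and any sensible meaning of main outcomes includes overweight and obesity. The t-test and chi-square sentence is in the past tense, follows the descriptive statistics, and also serves comparisons by overweight status. It may describe baseline tables only, and some of the named variables may belong to the weight-status comparison rather than to the arm comparison.

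Much of this stands. A reader might infer that the primary comparison ignores randomisation by school; the article does not support that. Nor does it establish that the secondary outcomes have no cluster-valid analysis, because the main outcomes could be defined broadly.

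The reply does not remove the point. Tense is a weak guide: the legend to Figure 1 reports the June 2014 measurements in the past tense, and the randomization section mixes past and future. The sentence sets no time point and speaks of blood sample outcomes. Overweight can hardly be compared by overweight status, so its chi-square test must be by arm. Even if only baseline was meant, student-level tests between randomised schools would flag imbalances too often.

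A fair objection also applies to the size. The ICC is assumed, and stratification would lower the inflation, as would smaller blood samples.

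**Conclusion.** The concern holds as a defect in what the paragraph states. It permits student-level tests of arm differences in a school-randomised trial, and it does not define the outcomes that the multilevel models protect. For the primary outcome the risk is ambiguity: two possible tests and no stated precedence. For any outcome outside the multilevel models the risk is an invalid test.

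Over an assumed ICC of 0.001 to 0.02, and ignoring stratification, the true size of a nominal 5% test is about 17% to 67% with 1,000 students per school and 12% to 59% with 625. The mildest of these cases still more than doubles the nominal error rate.

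Two stronger statements are not supported. A reader might say that such tests are wrong half the time, but that is true only near an ICC of 0.01. A reader might also say that spurious benefits are close to certain. Take 13 null secondary measures (waist, hip, blood pressure, skinfold, five blood and four fitness measures), treat them as independent, and count only errors that favour the intervention. The chance of at least one is 1 − (1 − 0.554/2)^13, about 98%, at a size of 55.4%. It is 1 − 0.94^13, about 55%, at a size of 12%. Correctly sized tests would already give 1 − 0.975^13, about 28%. Correlation between outcomes would lower these figures.

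**What to change.** Reword the quantitative analysis paragraph as follows:

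- Use t-tests and chi-square tests for no between-arm inference.
- Analyse every between-arm outcome, primary and secondary, with a regression model that has school as a random effect and adjusts for the baseline value.
- List the outcomes meant by the main outcome variables, and state that the multilevel model alone decides the primary result.
- Present baseline characteristics by arm descriptively, without significance tests.

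The cost is wording and modest extra programming, with no new data. Confidence intervals will be wider than the student-level ones, as they should be.

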### Specific objectives

To assess the effectiveness of the Health Lifestyles Interventions, in children and adolescent aged 7–18 years, by comparing in intervention and control schools:**Primary outcomes:** Change in the prevalence of overweight and obesity**Secondary outcomes:**Anthropometric outcomes: waist circumference, hip circumference, blood pressure and skin fold thickness;Behavioral outcomes: dietary, sedentary or PA behaviors and their determents (e.g. children’s or parental knowledge, beliefs and attitudes, parental BMI, PA and eating behaviors, school environment);Blood chemical outcomes: fasting plasma glucose, fasting triglycerides, total cholesterol, high-density lipoprotein cholesterol (HDL-C), low-density lipoprotein cholesterol (LDL-C);Physical fitness outcomes: standing-board jump, 50 meters speed run, 50 meters × 8 shuttle run (primary students) and run 800/1000 meters (secondary school students).2.To conduct a process evaluating by qualitative interviews and other methods to explore the way the interventions worked (that is, how it was delivered, taken up and experienced, and what the behavioral mediators of change are).

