### Randomization and blinding

Multistage cluster sampling was used. The random sequence of schools will be computer generated and stratified by (1) school district; (2) school grades (primary or high) and (3) school size in each center. All of the students in the selected schools of different grades, namely, grades 1 to 12, were invited to participate in the survey. After a school is confirmed to be eligible and both parents and children written informed consent have been obtained, it will be randomly assigned to intervention or control group. Intervention or control schools in the same stratification were allocated using simple random sampling method. Randomization will be performed by a member of staff who is not involved with the trial immediately after all schools have been recruited according to the standard.

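### The stated multilevel adjustment is the pre-test value; the factors that stratified the school randomisation are not named in it, which may cost precision or power

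*Protocol article*

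**What the plan says.** Under Randomization and blinding, the random sequence of schools is "computer generated and stratified by (1) school district; (2) school grades (primary or high) and (3) school size in each center". Allocation is then made inside those strata: "Intervention or control schools in the same stratification were allocated using simple random sampling method". The abstract gives a 1:1 ratio of intervention to control schools.

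Under Quantitative data analyses, the model for the main outcomes takes one sentence: "Multilevel regression models will be used to test for post-test group differences on the main outcome variables corrected for pre-test measurements". It names neither the levels of the model, the random effects nor the link, and no covariate other than the pre-test value. The same section also lists t-tests and chi-square tests for group differences. It calls none of these analyses primary.

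The primary outcome under Specific objectives is "Change in the prevalence of overweight and obesity", so the underlying variable is binary for each pupil. Sample size calculations gives 70 schools in 7 centres. Participants gives 12 to 16 schools per centre, which is 84 to 112 over the seven.

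**The concern.** Stratifying the randomisation balances the arms on centre, district, school level and size. That lowers the true variance of the treatment estimate if those factors are prognostic. The analysis benefits only if the factors are in the model. Otherwise their variation stays in the estimated between-school variance, the standard error is larger than the real sampling variability of the estimate, and the nominal 95% interval covers more than 95%.

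The sentence on the multilevel model is not silent about adjustment. It names an adjustment, and that adjustment contains none of the randomisation factors. Followed as written, the analysis does not match the design.

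Precision and power are at stake. There is no bias and no inflated type I error from this source. The number of schools limits precision here, and 70,000 pupils do not make up for between-school variance that the model could have removed.

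**Working it through.** **The plan's own figure.** The documents state no interval width, intraclass correlation or between-stratum variance, so there is no figure of theirs on this point to reproduce. The stated sample size ("the minimum number required would be 420 of each grade in each center", 90% power, two-sided 5%) cannot be derived from the design inputs because the control rate is missing. The nearest match found for 420 assumes an absolute fall from 15% to 5%: 207 per arm with continuity correction, or 414 in total, without any allowance for clustering. That figure does not bear on the question here.

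**Inputs.**
- Schools: 70 (Sample size calculations), or 98 as the midpoint of 84 to 112 (Participants).
- Centres: 7. School level: 2 classes (Randomization and blinding).
- School size: 2 classes. This is my assumption, since the number is not stated.
- f: the share of school-level variance remaining after pre-test correction that the strata explain. The documents do not give it, so it is varied from 0 to 0.50.

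**Formula (linear scale, school level).**

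width ratio = [t(0.975, df1) / t(0.975, df0)] × √(1 − f)

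Here df0 is for the pre-test-only model and df1 for the model with strata. With 70 schools, df0 = 70 − 3 = 67 (intercept, arm, pre-test). Main effects for centre, level and size use 6 + 1 + 1 = 8, so df1 = 59. All 7 × 2 × 2 = 28 cells use 27, so df1 = 40.

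- f = 0, main effects: 2.0010 / 1.9960 = 1.002.
- f = 0, 28 cells: 2.0211 / 1.9960 = 1.013.
- f = 0.10, main effects: 1.0025 × √0.90 = 0.951.

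| f | 70 schools, main effects | 70 schools, 28 cells | 98 schools, main effects |
|---|---|---|---|
| 0 | 1.002 | 1.013 | 1.001 |
| 0.05 | 0.977 | 0.987 | 0.976 |
| 0.10 | 0.951 | 0.961 | 0.950 |
| 0.20 | 0.897 | 0.906 | 0.895 |
| 0.30 | 0.839 | 0.847 | 0.838 |
| 0.50 | 0.709 | 0.716 | 0.708 |

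District is left out of this count because the number of districts is not stated. If each centre had two districts, the extra 7 contrasts would give df1 = 52 and a ratio at f = 0 of 2.0066 / 1.9960 = 1.005, so the picture is unchanged.

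**Check by simulation.** Stratified randomisation of 70 schools, linear school-level analysis of covariance, centre and school level as strata, 1,500 runs per setting:

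| f | Width ratio | Coverage, pre-test only | Coverage, with strata |
|---|---|---|---|
| 0 | 1.013 | 95.6% | 95.2% |
| 0.10 | 0.959 | 96.6% | 95.9% |
| 0.30 | 0.844 | 97.3% | 94.5% |
| 0.50 | 0.709 | 98.9% | 94.3% |

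The Monte Carlo standard error of a coverage near 95% is √(0.95 × 0.05 / 1500) = 0.6 points. The excess coverage at f = 0.30 and 0.50 is therefore well outside simulation noise.

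A separate simulation used 84 schools in 14 centre-by-level strata and 2,000 runs. At f = 0.50 the pre-test-only standard error averaged 0.559 points against a true standard deviation of 0.417 (0.559 / 0.417 = 1.34), with coverage of about 99%. Adding strata brought the standard error to 0.419, a cut of 25%.

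**The case against.** The strongest reply is that this is inferred from one sentence in a condensed article. The sentence does not say that adjustment stops at the pre-test value, the centre could be a level of the multilevel model, and a covariate list often sits in a fuller protocol or SAP. A reader might infer from the article that the strata are definitely excluded. The text does not support that. What stands is narrower: the article chose to name its adjustment, and what it names does not match its randomisation.

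A reader might also infer that the trial's intervals will be too wide as a matter of fact. That needs strata that predict outcome after pre-test correction, and the documents do not show this. The regional differences reported in the Discussion are largely differences in level, which the pre-test value is meant to absorb. On trend, the same paragraph points both ways: the steepest rises were in large coastal cities, yet rises elsewhere are called similar. Nothing in the article documents that weight change over nine months differs between children and adolescents. If f is near zero, the strata-adjusted interval is marginally the wider one.

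The scale also matters. The primary outcome is binary. In a logistic multilevel model, adding covariates moves the conditional odds ratio as well as its standard error, so the cost shows mainly as lost power. The percentages above apply to a linear school-level analysis.

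Finally, the model is not labelled primary. The t-tests and chi-square tests in the same section mention no clustering. Read as ignoring it, they would err the other way, so one cannot say that every interval in this trial will be too wide.

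**Conclusion.** The point holds in conditional form. Randomisation is stratified by district, school level and size within centre, and the stated model adjustment includes none of these. If the factors are prognostic beyond the pre-test value, leaving them out makes the inference conservative and less efficient; neither simulation showed it to be anti-conservative.

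The size cannot be computed from the documents. Under the assumed shares, including the strata changes the interval from about 0.2-1.3% wider (share 0) to about 4-5% narrower (10%), 16% narrower (30%) and 29% narrower (50%). This rests on a linear scale, 70 to 98 schools and two size classes. The possible loss from adding the factors is very small and the possible gain is material, so this is a cheap improvement worth making. It is not a flaw that threatens validity.

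**What to change.** State in the analysis section that the multilevel models for the main outcomes include a random intercept for school and, as fixed main effects, centre and the randomisation factors (school district, school level, school size), in addition to the pre-test value. Main effects are preferable to all cells: 70 schools over 28 cells is 2.5 per cell, before district is counted. Where strata are too sparse, keep at least centre and school level.

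The change is one sentence, and the variables were needed for the randomisation and so are already held. The price is a few school-level degrees of freedom: 8 of 67 for centre, level and size, plus those for district. If the factors explain nothing, the interval widens by about 0.2% with main effects for centre, level and size.

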#### Qualitative data analyses

All interviews will be audio-taped and transcribed verbatim. Transcribed data will be managed using NVivo 8.0 software which will also support the coding and analytical processes. All of the transcripts will be read and re-read in order to gain an overall understanding of participants' views and experiences. Thematic analysis and comparative analysis will be adopted for the analysis and interpretation.

